## Discussion

### Potential impact and significance of the study

Treatment adherence is critical to the success of ART and is largely determined by behavior. This study will test novel behavioral interventions to improve ART adherence and has the potential to enhance HIV treatment and prevention significantly. An increasing number of people have been on ART for many years (i.e., they are treatment-mature), and they may lack motivation to adhere to their medication consistently. This study will be one of the first that we are aware of that tests an intervention designed to increase the motivation of treatment-mature clients for adherence. The findings of this study will provide unique insight into the underlying behavioral mechanisms that affect HIV treatment adherence, which could be exploited to improve adherence in a variety of settings.

In addition, this study will test an intervention that is readily and cheaply scalable. While previous work by the study team has demonstrated that lotteries based on MEMS caps can be effective at encouraging adherence, this study will compare the efficacy of using measured adherence vs. viral load to determine lottery eligibility. While MEMS caps are relatively costly, viral load testing is now part of routine clinical care in Uganda and therefore, is available at no additional cost. We will test whether directly incentivizing viral suppression is as effective as incentivizing electronically measured adherence, and also conduct a cost-effectiveness analysis. This will help guide whether incentivizing viral suppression should be scaled up or whether the extra cost of the MEMS caps is worth the potential extra benefits of directly incentivizing adherence.

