**Discussion:**

Our study is one of the first to investigate the effectiveness of lottery incentives for improving ART adherence, and in addition, it compares the relative efficacy of using electronically measured adherence versus viral load to determine lottery eligibility. MEMS caps are relatively costly, whereas viral load testing is now part of routine clinical care in Uganda. BEST will test whether directly incentivizing viral suppression (which can be implemented using readily available clinic data) is as effective as incentivizing electronically measured adherence. Cost-effectiveness analyses of the two implementation modes will also be performed.

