##### Draws with small prizes at each scheduled clinic visit

Participants will be eligible to participate in prize draws whenever they come to the clinic as scheduled (roughly every 2–3 months). When a client assigned to T1 comes to the clinic, the study coordinator will check whether they have an appointment using the client’s clinic booklet and medical records. If the client does have an appointment, they are invited to draw a number out of a bag without looking. Each number corresponds to a different type of prize and they will have four prize options, as outlined in Table 1.

**Table 1 Tab1:** Prizes awarded at each clinic visit for treatment group 1

Prize	Value (USD)	Win probability
No prize	0	0.25
Small water bottle	0.50	0.25
Large water bottle	1.00	0.25
Umbrella or coffee mug	1.50	0.25

Altogether, 75% of clients will win something in each draw, which is meant to minimize the discouragement of not winning anything as observed in our previous work [45]. Clients will win the smallest prize worth about .50 with probability of 0.25, the medium – sized prize with value of 1 with a probability of 0.25, and the largest prize valued at $1.50 with a probability of 0.25.

As in previous studies, we sometimes observed that there was a discrepancy between the scheduled appointment date in the client’s booklet and the medical records. We will let them enter into one draw a year when they arrive for what their booklet says is an appointment but which has been wrongly entered into the system, but it will be made clear to the client that this is a one-time exception only.

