### Sample size and power

We have calculated the size of effects that our sample will be able to detect with 80% power (two-tailed test) with regard to outcomes at months 12 and 24, and 10% attrition every year (we observed 5% attrition over 20 months in our previous studies so this is a conservative estimate). For the primary outcome of viral suppression, we use a conservative estimate of 70% of clients in the control group showing suppression, based on discussions with the Mildmay team. Our sample size of 110 participants in each of the three arms (total *n* = 330) will be able to detect a 7 percentage point difference for joint comparison of T1 and T2 against the control group at month 12, and about an 8.5 percentage point difference between the two intervention arms (a subgroup analysis). The corresponding differences at month 24 are 8 and 9 percentage points, respectively. These are considered small effect sizes (Cohen’s *d* of between .15 and .185), which we will be able to detect. For adherence, in our previous study we observed mean adherence rates of ~75% as measured by MEMS caps. Our sample size of 110 in each of the intervention arms and the control group will provide sufficient power to detect about a 6.5 percentage point difference in mean adherence between the two intervention arms (combined) and the control group. To test for differences in adherence between the two intervention arms, our study is powered to detect about a 7.5 percentage point effect as measured by MEMS caps. Again, this means we will be able to detect small effects. The corresponding differences we will be able to detect at month 24 are about 7 and 8 percentage points, respectively. Our main econometric models will include covariates that will improve precision. Therefore, these minimum detectable effects reported above are likely upper bounds.

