##### Estimating impact on viral suppression

We will use a logistic regression to compare the likelihood of viral suppression between the three study arms after year 1 and after year 2. We will estimate an unadjusted model and a model that includes prespecified covariates to adjust for baseline characteristics and improve precision. We will adjust for the following covariates: age, education, sex, baseline adherence, baseline WHO disease stage, baseline viral suppression, duration on ART, self-reported physical health, self-reported mental health, and HIV disclosure status.

Our main unadjusted model has the following form:
1$$ \Pr \left({y}_i\right)=\mathrm{expit}\left({\beta}_0+{\beta}_1T{1}_i+{\beta}_2T{2}_i+{\epsilon}_i\right) $$

and our main adjusted model has the following form:
2$$ \Pr \left({y}_i\right)=\mathrm{expit}\left({\beta}_0+{\beta}_1T{1}_i+{\beta}_2T{2}_i+{\boldsymbol{X}}_{\boldsymbol{i}}{\boldsymbol{\beta}}_{\mathbf{3}}+{\epsilon}_i\right) $$

where *y*_*i*_ is the probability of viral suppression of individual *i*, T1 is an indicator for treatment group 1, T2 is an indicator for treatment group 2, and *ϵ*_*i*_ is the idiosyncratic error. The coefficients of interest are *β*_1_ and *β*_2_. Equation 2 has the term ***X***_***i***_***β***_**3**_, which includes a vector of the prespecified covariates described above (***X***_***i***_) and the respective coefficients (***β***_**3**_). We will estimate the marginal difference (or risk difference) between each of the three study arms as the following:
$$ \mathbbm{E}\left[{y}_i\right|T1=1\left]-\mathbbm{E}\left[{y}_i\right|\mathrm{Control}=1\right] $$: Impact of treatment 1 on the outcome relative to the control group$$ \mathbbm{E}\left[{y}_i\right|T2=1\left]-\mathbbm{E}\left[{y}_i\right|\mathrm{Control}=1\right] $$: Impact of treatment 2 on the outcome relative to the control group$$ \mathbbm{E}\left[{y}_i\right|T2=1\left]-\mathbbm{E}\left[{y}_i\right|T1=1\right] $$: Impact of rewarding adherence relative to rewarding viral suppression

We will also estimate a model where we pool T1 and T2 (relative to the control group) to estimate the impact of lottery incentives more generally.

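### The aim of showing that T1 is as effective as T2 rests on a two-tailed difference comparison, which cannot support a claim of comparable effectiveness

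*Protocol article*

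**What the plan says.** The aim is stated twice. The abstract's discussion reads "BEST will test whether directly incentivizing viral suppression (which can be implemented using readily available clinic data) is as effective as incentivizing electronically measured adherence". The section on potential impact repeats it ("We will test whether directly incentivizing viral suppression is as effective as incentivizing electronically measured adherence") and adds that the result will help to guide whether the viral-load lottery is scaled up or the extra cost of MEMS caps is worth paying.

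The analysis of suppression lists three risk differences from a logistic model. The third is T2 minus T1, labelled "Impact of rewarding adherence relative to rewarding viral suppression". No margin accompanies it.

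The sample size section works "with 80% power (two-tailed test) with regard to outcomes at months 12 and 24, and 10% attrition every year". For suppression, "we use a conservative estimate of 70% of clients in the control group showing suppression". It then gives the detectable T1 versus T2 difference at month 12 as "about an 8.5 percentage point difference between the two intervention arms (a subgroup analysis"), and 9 points at month 24.

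On what T1 rewards, the abstract and the description of the study interventions name two conditions: timely visits or refills, and viral suppression. For the visit draws, "Participants will be eligible to participate in prize draws whenever they come to the clinic as scheduled". Suppression governs one larger draw a year.

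**The concern.** A claim that one arm is as effective as another is a claim that any deficit is too small to matter. A difference test does not address that. Non-significance shows only that the data did not exclude zero, and in a small trial that is compatible with a large deficit.

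The T1 versus T2 comparison carries the practical message of the trial, because T1 needs no MEMS caps to run and is the cheaper mode. If a null T2 minus T1 result were taken as comparability, T1 could be favoured while being materially worse. The sample size section adds to this risk: a reader who trusts its figures would think that a null result makes a deficit of about 9 points unlikely.

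**Working it through.** **Inputs.** 110 per arm, 1:1:1 (Randomization; Sample size and power). "10% attrition every year" gives 110 × 0.90 = 99 per arm at month 12 and 110 × 0.81 = 89 at month 24. The control suppression rate is 70%; no rate is given for T1 or T2, so 70 to 80% is used as a range. Alpha is not stated; two-sided 0.05 is assumed.

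**1. The plan's own figure.** Power for two proportions by the normal approximation is

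Φ{(d − 1.96·SE0) / SE1}, with SE0 = √[2·p̄(1−p̄)/n] and SE1 = √[(p1(1−p1) + p2(1−p2))/n].

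Solving for 80% power upward from 70%:

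| Evaluable per arm | Detectable difference, recomputed | Stated |
|---|---|---|
| 110 (no attrition) | 15.6 points | – |
| 99 (month 12) | 16.4 points | 8.5 |
| 89 (month 24) | 17.1 points | 9 |

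The stated figures do not reproduce; one-sided, the result is still 14.0 to 15.4 points. Detecting 8.5 points would need about 415 evaluable per arm, and 9 points about 367. Power at the stated differences is about 28% (70 vs 78.5 with 99 per arm; 70 vs 79 with 89 per arm).

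**2. Width of the interval for T2 − T1.** Half-width = 1.96·√[2p(1−p)/n], unadjusted, both arms at p:

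| n per arm | p = 70% | p = 80% |
|---|---|---|
| 99 | ±12.8 | ±11.1 |
| 89 | ±13.5 | ±11.8 |

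**3. Chance of missing a real T1 deficit.** The 10-point deficit is an illustration, not a figure from the documents. For T1 70% and T2 80%:

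- n = 99: SE0 = 0.0615, SE1 = 0.0611; (0.10 − 1.96 × 0.0615)/0.0611 = −0.34; power 36.8%, missed 63%.
- n = 89: SE0 = 0.0649, SE1 = 0.0645; (0.10 − 1.96 × 0.0649)/0.0645 = −0.42; power 33.6%, missed 66%.

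For 60% vs 70% the miss rate is 69% and 71%.

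**4. Chance of excluding a 10-point deficit when the arms are equal.** Power = Φ{0.10/√[2p(1−p)/n] − 1.96}:

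- n = 99: 34% (p = 70%) to 42% (p = 80%).
- n = 89: 31% to 39%.

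For 80% power at that margin, 252 to 330 evaluable per arm would be needed.

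**5. Covariate adjustment.** If the covariates removed 30% of the outcome variance, power for a 10-point deficit would rise only to about 39 to 49% (T2 rates of 70 to 80%). They would have to remove about 72 to 73% of the variance to reach the stated 8.5 and 9 points.

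**6. What T1 pays for (secondary).** Each visit draw is worth 0.25 × (0 + 0.50 + 1.00 + 1.50) = USD 0.75. One draw every 2 to 3 months is 4 to 6 a year, or USD 3.00 to 4.50. The annual suppression draw is 0.10 × USD 10 = USD 1.00. Scheduled visits therefore carry 3.00/4.00 = 75% to 4.50/5.50 = 82% of expected prize value for a client who is always suppressed.

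**The case against.** **No decision rule is stated.** A reader might infer that the investigators will treat a non-significant T2 − T1 result as equality. The article does not say so. It plans to estimate a risk difference, also speaks of comparing relative efficacy, and ties scale-up to a cost-effectiveness analysis whose intervals use the confidence limits of the effect. This stands, so the point is a mismatch between aim and comparison, not a declared misuse of a p-value.

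**A margin may sit in the full protocol or SAP.** It may. But the article itself fixes both the question and the two-tailed powering, and as stated the second does not answer the first.

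**Small margins might seem impossible to meet.** The half-widths could suggest that no margin below about 13 points can be met. That is not so: meeting a margin depends on the observed difference as well as the width, and step 4 gives 31 to 42% power for 10 points. It is underpowered, not impossible.

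**The widest half-widths are a worst case.** They put both incentive arms at the control rate of 70% and ignore adjustment. This is fair, which is why a range is shown and the adjusted case is given.

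**The T1 label is shorthand.** The article discloses both conditions, and T2's visit draws also take place only at scheduled visits. Expected value may understate the pull of a USD 10 prize, since the article itself argues that people overestimate small probabilities. So a reader should not infer that T1's composition is hidden, or that suppression is a negligible part of it. Only the wording of the contrast and conclusions is at issue.

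**Conclusion.** The concern holds as a mismatch between the stated aim and the planned comparison. A two-tailed T2 − T1 difference cannot by itself support a claim that T1 is as effective as T2. At the planned size the uncertainty on suppression is large: about ±11 to ±13.5 points unadjusted, with a 70% vs 80% deficit missed 63 to 66% of the time. Adjustment would narrow this somewhat. The 8.5- and 9-point detectable differences recompute to about 16 to 17 and should not be used to interpret a null result.

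These figures assume a two-sided alpha of 0.05, 10% attrition a year, suppression of 70 to 80% in the incentive arms, and a normal approximation. The 10-point deficit and margin are illustrative. Adherence could not be checked because the article gives no standard deviation. The T1 label is a secondary wording point.

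**What to change.** - State that a non-significant T2 − T1 difference will not be read as equal effectiveness.
- For both primary outcomes, report T2 − T1 with its 95% interval against a margin named before unblinding. Claim that T1 is as effective only if the interval excludes a T1 deficit of that size.
- State that power to meet a margin near 10 points on suppression is low, about 31 to 42% if the arms are truly equal.
- Recompute or withdraw the 8.5- and 9-point figures, and do not use them to interpret a null result.
- In the contrast label and the conclusions, describe T1 as timely visits or refills plus viral suppression, in line with the abstract and the description of the interventions.

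The cost is wording, one interpretation rule and agreement on a margin; neither design nor sample size changes. The downside is that the trial may have to report comparability as unsettled.

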### Reporting adverse events

While we are doing everything to avoid increasing the risk to study participants due to any study-related activity, we will be very careful in tracking any potential negative events experienced by any study participant. Adverse events relating to ancillary and post-trial care may encompass both physical and psychological harms. The study coordinator will be experienced and trained to recognize risks or crises that require referrals. Team members have established procedures and guidelines to respond to risk disclosures and crisis situations among participants. If there are indications during a study visit that a participant poses a risk of suicide or self-harm, the interviewer will stop the session and explain to the participant that they would like an on-site Mildmay mental health counselor to speak with the participant about the situation. The counselor will then assess the risk for potential harm and the appropriate action in terms of evaluating the client’s need for mental health services and notifying the appropriate authorities. This assessment should be done as soon as possible and before the client leaves the premises, to the extent possible. A serious adverse event report will be filed, if necessary. Everything will be done immediately if possible and certainly within 24 h.

Anything that looks like it could be an adverse event will be brought to the attention of the local and study PIs, since each case needs to be investigated. Any unexpected or serious adverse events that occur during the course of this investigation and follow-up period will be reported by telephone by the PI within the next business day to the study institutional review boards (IRBs) and the independent study monitor. The telephone report will be followed within 3 business days by a written report, which will contain: the subject’s ID, the title and date of the serious adverse event, and a narrative explanation (e.g., how the research staff was notified of the event, dates of consent, screening results for inclusion or exclusion, whether the participant participated in the intervention or was in the control group, dates and circumstances of the hospitalization or death, and the participant’s status at their last clinical or research contact). In consultation with the IRBs, the PI will address whether there is a need to redesign or amend the protocol, or to inform current and future subjects of a change in how risks are described (e.g., changes to the consent form or protocol).

Except for adverse events, we do not expect that the interventions will need to be discontinued for any reason. As per our IRB protocol, participants are free to withdraw from the study at their own discretion. Due to the low-risk nature of the intervention, there will be no interim analyses or stopping rules.

### Dissemination of results

Study findings will be disseminated to researchers and clinicians via peer-reviewed publications and conference presentations. Published papers will follow established guidelines for defining the level of contributions that warrant authorship. Our findings will be relevant to local Ugandan and global communities with an interest in understanding the underlying behavioral mechanisms that affect HIV treatment adherence. We will share these findings with senior officials at the Ministry of Health and at Mildmay Uganda, so they can formulate appropriate policies in line with the national recommendations on annual viral load screenings for HIV-positive patients.

### Limitations

This study has several limitations. First, the study will include only 330 patients from one clinic in Uganda. Although our sample size is well powered to detect clinically important effects, it is not clear that our results will extrapolate to other areas of Uganda or other countries. Second, while our study includes both large and small incentives, we are unable to disentangle the effect of these different incentive types and the extent to which there is a dose response with incentive size. The impact of offering different incentive types and amounts will require further research. We also cannot verify the longer-term effects of these incentives or whether any effects persist after the incentives are withdrawn beyond the 12-month period during which we will monitor the effects of the intervention. Third, although adherence is measured using MEMS caps, which is currently one of the most accurate ways to measure adherence, we cannot exclude the possibility that some participants will consciously manipulate the pill bottle openings to increase their chances of receiving the incentives. 

### Trial status

The trial registration number is NCT03494777. The study start date was 12 April 2018. The protocol reported here is dated 17 October 2018. Patient recruitment is currently underway. The primary completion date is 1 March 2022 and the study completion date is 1 July 2022.

## Data Availability

External researchers interested in our data, survey instruments, and other research methodology and procedures will be able to obtain this information through collaborative agreements (e.g., data use agreements) with the PI and co-investigators, as required by the data-sharing policy of the National Institutes of Health.

## Abbreviations

ART: Antiretroviral treatment
BEST: Behavioral Economic Incentives to Support HIV Treatment Adherence study
HIV: Human immunodeficiency virus
ICER: Incremental cost-effectiveness ratio
IRB: Institutional review board
MEMS: Medication event management system
NGO: Non-governmental organization
PI: Principal investigator
T1: Treatment group 1
T2: Treatment group 2
